#### Safety measurements

Any possible accidental injuries caused by this study will be prevented as much as possible, the relevant medical expenses will be covered by the research project team, and the participants will receive certain financial compensation. Any unexpected adverse events during the intervention period will be monitored and reported to a research assistant. Causality in relation to the acupuncture intervention and the severity of adverse events will be analyzed. Serious adverse events will be reported to the ethics committee.

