### Objectives

The main purpose of this multicenter study is to verify the efficacy and safety of acupuncture treatment for episodic memory impairment in patients with aMCI through a randomized controlled trial and then explore its neuroimaging mechanism through functional magnetic resonance imaging (fMRI) and electroencephalogram (EEG).

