### Outcome assessment

The variables in this trial consist of demographics and clinical characteristics, primary outcomes, and secondary outcomes. The basic characteristics will be measured at baseline (1–2 weeks before randomized allocation). Primary and secondary outcomes will be measured at baseline, the middle of intervention (4 weeks), the end of intervention (8 weeks), and 4 weeks of follow-up. Outcomes of fMRI and EEG will be measured at baseline and the end of intervention (8 weeks). All outcomes will be evaluated by experienced doctors who will be blinded to the allocation results of participants. A summary of all measurements in this trial is shown in Table 2.

**Table 2 Tab2:** Trial processes chart

Study period Item	Enrolment and Baseline	Intervention Period (8 weeks, one time per 4 weeks)				Follow-up phase
**Week**	-2 to 0	1 to 3	4	5 to 7	8	12

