**Safety**						
Adverse events		×	×	×	×	×
Reasons for dropout and withdrawals		×	×	×	×	

*TSYZ* Tiaoshenyizhi, *GDS* Global Deterioration Scale, *BDI* Beck Depression Inventory, *MoCA* Montreal Cognitive Assessment, *AVLT-H* Auditory Verbal Learning Test-Huashan version, *TMT* Trail Making Test, *DSST* Digit Span Subtest, *SF-36* Medical Outcomes Study 36-item short form health survey, *EEG* Electroencephalogram, *fMRI* Functional magnetic resonance imaging

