### Statistical analysis

Statistical analysis will be performed using SPSS software V.26.0 (IBM) package by an independent statistician, with a statistical significance of *P* value < 0.05 on both sides. Categorical variables will be described as frequencies or percentages using a chi-square test. For the normal distribution, continuous variables will be expressed using mean ± standard deviation (SD) and will be assessed by one-way analysis of variance (ANOVA) and compared between every group. For non-normal distribution, continuous variables will be expressed using the median and its interquartile range (IQR) and be analyzed by the rank sum test. The missing data will be filled in using the multiple imputation method. When baseline index imbalances occur among the three groups, a general linear model or logistic regression model will be applied for the calibration and analysis.

Adverse effects (AEs) will be analyzed using a Chi-square test or Fisher’s exact test. If the formal statistical analyses between groups cannot be performed due to the lack of power, AEs will be tabulated and summarized using descriptive statistics. For fMRI data, DPABI (a toolbox for Data Processing & Analysis for Brain Imaging, Version 2.3_170105, http://rfmri.org/dpabi) software package will be used to preprocess the image data obtained by fMRI scanning under the Matlab2013a (The Match Works, Inc). Independent component analysis (ICA) will be used to extract time signals for sequence dynamic causal modeling (DCM) analysis. Components will be extracted from the preprocessed images using GIFT v4.0 (http://icatb.sourceforge.net/).

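### The safety text monitors *unexpected* adverse events up to week 8, while Table 2 schedules all adverse events to week 12 and the analysis compares them without either limit

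*Protocol article*

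**What the plan says.** All references are to the protocol article.

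- **Objectives.** Safety is part of the main purpose, which is to "verify the efficacy and safety of acupuncture treatment for episodic memory impairment in patients with aMCI".
- **Safety measurements.** The sentence on collection reads "Any unexpected adverse events during the intervention period will be monitored and reported to a research assistant". The next sentence, on causality and severity, speaks of adverse events without that qualifier.
- **Outcome assessment.** The schedule includes "the end of intervention (8 weeks), and 4 weeks of follow-up", so the intervention period closes at week 8 and follow-up runs to week 12.
- **Table 2.** The row "Adverse events" has no qualifier. It is marked in all five columns after baseline, the last being week 12. The row "Reasons for dropout and withdrawals" is marked in four columns and is blank at week 12.
- **Statistical analysis.** "Adverse effects (AEs) will be analyzed using a Chi-square test or Fisher’s exact test", with descriptive tables as the fallback. No limit to unexpected events or to the first 8 weeks is stated.
- **Discussion.** The article says that a full evaluation of adverse events is feasible.

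**The concern.** The collection rule, the schedule and the analysis should describe the same set of events, and here they do not. A site that follows the safety text would stop at week 8 and might screen out anything foreseeable. A site that follows Table 2 would record everything to week 12. With six centres, collection could differ from one to another.

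The qualifier matters because of how the two needling arms differ. Real needles are inserted, while the sham needle retracts and does not pierce the skin. Reactions to penetration are foreseeable, and they are the kind of event in which the two arms would be expected to differ. A rule that passes only unexpected events would remove much of that contrast before the chi-square or Fisher test is run. Since safety belongs to the stated main purpose, a finding of no difference would then be hard to interpret.

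**Working it through.** There is no stated figure to reproduce. The check sets the passages side by side.

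| Place in the article | Which events | Until when |
|---|---|---|
| Safety measurements, collection sentence | unexpected | end of intervention (week 8) |
| Safety measurements, causality and severity sentence | no qualifier | not stated |
| Table 2, adverse-event row | no qualifier | week 12 |
| Statistical analysis | no qualifier | not stated |
| Discussion | no qualifier, full evaluation | not stated |

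**Period.** The text covers weeks 1 to 8 and the table covers weeks 1 to 12. The disputed part is 12 − 8 = 4 weeks, and 4 / 12 is one third of the scheduled period. The week-12 mark is unlikely to be a fault of text extraction, because the row beneath it has one mark fewer and stops at week 8. This conflict does not depend on how *unexpected* is read.

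**Type of event.** Only the collection sentence carries the qualifier. An analysis of all adverse events cannot rest on a collection rule that passes only some of them, so either the sentence or the other places must change.

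**Direction of a possible bias.** This step assumes that the collection sentence is applied literally.
1. The TSYZ acupuncture group section has needles inserted and manipulated for at least 30 s.
2. The Sham acupuncture group section has a blunt needle that does not penetrate.
3. Reactions to penetration are therefore likelier in the real arm, and they are foreseeable.
4. Excluding them lowers the count more in the real arm than in the sham arm, so the difference shrinks.

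**Size.** Estimating the bias would need event rates by arm and the share of events judged foreseeable. The documents give neither.

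**The case against.** The strongest reply is that *unexpected* is loose wording, perhaps for untoward. Every other mention of adverse events is unqualified, and the sentence does not say that other events are ignored. This stands in part. It means that a reader who infers that expected needle reactions will go unrecorded goes beyond the text. It does not remove the period conflict, nor the need to correct a sentence that can be followed literally.

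A second reply is that a journal article leaves event definitions, lists of expected reactions and form content to the full protocol. That is right, and the absence of such a list is not criticised here. The point rests on statements that the article does make and that disagree.

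A third reply is that the two parts of the conflict are largely separate. Needling ends at week 8, so acute bleeding, bruising or needle pain would arise mostly inside the period that the text covers. This stands: the missing weeks 9 to 12 add little to the argument about needle reactions. The sham is also described as giving a pinprick-like feeling, so discomfort is not confined to the real arm.

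A fourth reply concerns the remedy. Asking at every contact would ascertain events unequally: the needling arms have 24 sessions, while health education takes place once every 4 weeks, which is 8 / 4 = 2 sessions in the intervention period. Questions about bruising could also unblind the outcome evaluators. This stands and shapes the fix below.

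**Conclusion.** The concern holds as an internal inconsistency with a possible consequence. The safety text, Table 2 and the analysis text disagree on which adverse events count and for how long. The period conflict is firm and covers 4 of 12 weeks. The conflict over type is firm as written, but its effect is conditional: if sites apply the sentence literally, the comparison of adverse events could be biased towards no difference, by an amount that cannot be estimated from the documents.

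Two further inferences are tempting and are not supported.

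- **Needle count as a measure of lost events.** Table 1 implies 4 + 1 + 5 × 2 = 15 needles per session, hence 15 × 24 = 360 per participant and 360 × 120 = 43,200 in the real arm. That is exposure at full attendance, while the sample size section allows for 20% loss. It says nothing about how many events would be missed.
- **Damage to the imputation.** The blank week-12 cell for dropout reasons might seem to weaken the handling of missing data. The Statistical analysis section states only that multiple imputation will be used and gives withdrawal reasons no role in it. The blank cell is a minor table point, worth correcting because the scales are measured at week 12.

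**What to change.** 1. In Safety measurements, delete *unexpected* and extend the period to week 12, so that all adverse events, expected or not, are recorded in all three arms. Align Table 2 and the Statistical analysis section with that sentence.
2. Base the between-group comparison on events asked about at the common time points, weeks 4, 8 and 12, in the same way in every arm. Have staff other than the blinded outcome evaluators ask.
3. Tabulate events noted at needling sessions separately, since the control group has no such sessions.
4. In Table 2, mark week 12 in the row for dropout and withdrawal reasons.

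The cost is slightly more recording work at contacts that already take place, staff other than the evaluators to ask the questions, and a higher reported event rate. The correction is best made promptly: the Trial status section reports 37 participants recruited by 12 August 2022, and events not recorded at the time are hard to recover later.

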**Methods:**

In this multicenter, parallel-group, double-blind, randomized controlled trial, 360 aMCI participants will be recruited from six subcenters and randomly assigned to the acupuncture group, sham acupuncture group, and control group. The acupuncture group will receive *TiaoshenYizhi* (TSYZ) acupuncture, the sham acupuncture group will use streitberger sham acupuncture, and the control group will only receive free health education. Participants in the two acupuncture groups will receive real acupuncture treatment or placebo acupuncture three times per week, 24 sessions over 8 consecutive weeks. The primary outcome will be global cognitive ability. Secondary outcomes will be a specific cognitive domain, including episodic memory and execution ability, electroencephalogram, and functional magnetic resonance imaging data. Outcomes will be measured at baseline and the fourth and eighth weeks after randomization. Repeated measurement analysis of variance and a mixed linear model will be used to observe the intervention effect.

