The characteristics of acupuncture treatment make it difficult to implement the double-blind method; therefore, we will blind participants by setting up the sham acupuncture group as a placebo [28, 50]. Considering the placebo effect of sham acupuncture, the health education group will be set up as a negative control group, providing prevention knowledge of common geriatric diseases, including AD. We increased the sample size and expanded the scope of the crowd compared with our previous research. The intervention can be implemented in community medical centers, and the adverse events can be fully evaluated. The main challenge of this study is whether such a large number of patients with aMCI are willing to receive acupuncture treatment until the end of the study and cooperate with the collection of each outcome. We will give material rewards to the participants.

In conclusion, through this study, the effectiveness of TiaoshenYizhi acupuncture on the episodic memory of patients with aMCI will be further clarified. We expect that this study will provide a reference for early treatment of aMCI and AD. The results of the study will be reported according to the guidance of the Consolidated Standards of Reporting Trials statement (STRICTA) [51].

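### The safety text and Table 2 disagree on which adverse events are captured and for how long, so the ascertainment rule is ambiguous and should be reconciled

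*Protocol article*

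**What the plan says.** Safety shares the main purpose of the trial with efficacy: the Objectives section sets out to "verify the efficacy and safety of acupuncture treatment for episodic memory impairment".

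The only prose on how adverse events are picked up is in Safety measurements: "Any unexpected adverse events during the intervention period will be monitored and reported to a research assistant". Two further statements in that section carry neither the word *unexpected* nor a time limit: "Causality in relation to the acupuncture intervention and the severity of adverse events will be analyzed" and "Serious adverse events will be reported to the ethics committee".

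Table 2 has a safety row headed "Adverse events", unqualified, with marks in every column after baseline, including week 12.

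The Statistical analysis section plans a chi-square or Fisher's exact test on adverse effects, or descriptive tables if power is lacking, and does not limit these to unexpected events or to the treatment weeks. The Discussion says that "the adverse events can be fully evaluated".

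**The concern.** The monitoring sentence carries two limits that the rest of the article does not share.

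The first is the window. Monitoring is tied to the intervention period, although the schedule collects adverse events at the follow-up visit after treatment has ended.

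The second is scope. Monitoring is tied to events that are unexpected. Some reactions to needling are foreseeable, and a person applying the word literally could decide that these need not be reported.

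The scope limit would not act equally across arms. By the article's own description, the sham needle is blunt and retracts without entering the skin, and the control group receives health education only. Reactions to skin penetration therefore arise in the acupuncture arm. A filter that removes foreseeable reactions would mostly remove them from that arm and shrink any true difference in event rates. In a trial that names safety in its main purpose, that could make the treatment look better tolerated than it is.

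**Working it through.** The protocol article states no figure that could be reproduced here, so the check sets its passages side by side.

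**Inputs**

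- Length of treatment: "24 sessions over 8 consecutive weeks" (Abstract, Methods).
- Follow-up: assessments at "the end of intervention (8 weeks), and 4 weeks of follow-up" (Outcome assessment), so the last visit is at week 12.
- Table 2 columns: weeks -2 to 0, 1 to 3, 4, 5 to 7, 8 and 12.

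**Step 1: window.** In Table 2 the adverse-event row is blank at baseline and then has five marks. Five marks in the five post-baseline columns put the last one at week 12. The row below it, on reasons for dropout and withdrawal, has four marks and stops at week 8. The week-12 mark is therefore specific to adverse events and is not just a repeated row pattern.

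| Source | Window | Scope |
|---|---|---|
| Safety measurements, monitoring sentence | intervention period, weeks 1 to 8 | unexpected events |
| Safety measurements, causality and severity | none stated | adverse events |
| Safety measurements, report to ethics committee | none stated | serious adverse events |
| Table 2, safety row | weeks 1 to 12 | adverse events |
| Statistical analysis | none stated | adverse effects |
| Discussion | none stated | adverse events, full evaluation |

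The disputed part of the window is 12 - 8 = 4 weeks, and 4 / 12 is one third of the period that Table 2 covers.

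**Step 2: scope.** The monitoring sentence is the only row of the comparison that says *unexpected*. If capture were limited in that way, the unrestricted analysis of causality, severity and between-arm frequency would rest on a narrower record than its wording implies, and the full evaluation mentioned in the Discussion could not be delivered.

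**Step 3: direction, if the monitoring sentence is followed literally.**

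- Penetrating needles are used in one arm of three (Interventions), so foreseeable reactions to penetration arise there.
- The acupuncture arm is deliberately needled until soreness, numbness, distention or heaviness is felt. These sensations are intended and are not adverse events in themselves, but staff who use expectedness as the test could set aside persistent soreness or numbness on the same ground.
- The section on randomisation and blinding says that acupuncturists and intervention supervisors know the allocation. The article does not say who judges expectedness; if they do, they judge it unblinded.

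These points argue for under-recording mainly in the acupuncture arm and so for a comparison pulled toward no difference. They concern the scope limit. Local reactions arise at sessions, which end by week 8, so the window limit adds little to that mechanism. It puts at risk late or persisting events in any arm, and the document gives no ground for assigning that loss a direction.

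**Step 4: size.** The article gives no rate for any adverse event, so neither the number of events affected nor the amount of bias can be computed from it.

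**The case against.** The strongest reply is that the article, read as a whole, intends to collect all adverse events. Table 2 schedules them without qualification and includes week 12. Causality, severity, the report to the ethics committee and the planned tests are all unrestricted. The monitoring sentence does not say that other events go unrecorded; the word *only* is not in it. The article lists no expected needling reactions, and *unexpected* may be loose wording for *untoward*. Definitions and collection rules are commonly left to the full protocol and the case report form.

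Much of this stands. A reader might infer that expected reactions and week-12 events are excluded from the record and that the safety comparison is therefore biased. The document does not support that. It follows only if the monitoring sentence overrides Table 2, and nothing says that it does. The missing list of expected reactions is no fault in a condensed article.

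A reader might also want to put a number on the loss. The acupuncture arm has 120 x 24 = 2,880 planned sessions, and an assumed reaction rate of 1% to 10% of sessions would give about 29 to 288 events. That range cannot be used as an estimate. The rate is not in the document, and the count also assumes that every session is delivered, that every reaction is classed as expected, and that none is recorded despite Table 2.

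What the reply does not remove is the contradiction. This is not a detail left to a fuller document: the article states a restrictive rule in one place and a wider one in another. With six centres, staff could follow either, and events not noted at the time are hard to recover.

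**Conclusion.** The point holds as an internal contradiction on adverse-event capture. The safety text and Table 2 differ in window (weeks 1 to 8 against weeks 1 to 12) and in scope (unexpected events against all), and the article does not say which governs.

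The consequence is conditional. If sites follow the safety text literally, foreseeable needling reactions could go unrecorded, mainly in the acupuncture arm, and events in weeks 9 to 12 could be missed. The between-arm safety comparison could then be biased toward no difference. If sites follow Table 2, neither limit applies and this bias does not arise. The conclusion assumes that foreseeable reactions come mainly from skin penetration, which fits the article's description of the three arms. The size is unknown.

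The efficacy analysis is not affected. Because safety is in the main purpose and the correction is small, it should be made.

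**What to change.** Reconcile the monitoring sentence in Safety measurements with Table 2. It should state that all adverse events, expected or unexpected, are recorded in all three arms from randomisation to week 12. Starting at randomisation, and not at the first needling session, gives the un-needled control group the same start point. Keep expectedness only as an attribute recorded for each event, not as a condition for recording it. Carry the same rule into the case report form instructions at all six centres.

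The cost is one sentence and slightly more event entry. No visit is added, because Table 2 already schedules these contacts, and no treatment rule changes. The article reports 37 of 360 participants recruited on 12 August 2022, so a clarification at that stage would cover most of the safety data. For participants already enrolled, the centres should confirm which rule they applied.

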### Sample size

MoCA score of the cognitive function assessment scale will be used as an effect index to evaluate the recovery of cognitive function in patients with MCI. According to the previous study and clinical experience, it has been estimated that the MoCA score difference between the elderly with MCI and the baseline after eight weeks of acupuncture was 5.50 ± 2.48 points, and the MoCA score difference of the control group was 4.88 ± 2.45 points [37]. On this basis, the calculated effect quantity is 0.17, and by the two-sided test, α = 0.05, β = 0.20, calculated by gpower 3.1.9.2 software, and the sample size is 300 cases. Considering the loss of follow-up rate of 20%, the total sample size of this study is 360 cases, i.e., 120 cases in each group.

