## Methods and analysis

### Study design

The design of this study is a randomized controlled trial, strictly following the Standard Protocol Items: Recommendations for Interventional Trials (SPIRIT) statement (see Additional file 1) [25]. The allocation will be hidden, and the allocation ratio will be 1:1:1. A total of 360 eligible participants will be randomly assigned to the TiaoshenYizhi acupuncture group, the sham acupuncture group, and the control group. Participants will be evaluated at baseline (weeks -2 to 0) and weeks four, eight, and 12. EEG will be used to explore the diagnostic value of event-related potential (ERP) in aMCI, and fMRI will be used to measure the structure and function of brain regions related to episodic memory at baseline and eight weeks. All data collectors will not know the group assignment. The research procedure and results evaluation schedule of this trial are shown in Fig. 1 and Table 1.

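### The effect size of 0.17 does not follow from the means and SDs it is said to come from; at the assumed 0.62-point difference, power is about 33–43%, not 80%

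*Protocol article*

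**What the plan says.** All the inputs are in the protocol article, section Sample size. The expected eight-week MoCA gain "after eight weeks of acupuncture was 5.50 ± 2.48 points", and "the MoCA score difference of the control group was 4.88 ± 2.45 points". The next sentence draws the effect size from these figures: "On this basis, the calculated effect quantity is 0.17". The test settings are "by the two-sided test, α = 0.05, β = 0.20", and the result is "calculated by gpower 3.1.9.2 software, and the sample size is 300 cases". This is then raised for attrition: "Considering the loss of follow-up rate of 20%, the total sample size of this study is 360 cases, i.e., 120 cases in each group".

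The section does not say whether 0.17 is a d or an f, which G*Power test was run, or what mean was assumed for the sham arm. Under Study design, "the allocation ratio will be 1:1:1" across three arms. Under Statistical analysis, normally distributed continuous outcomes "will be assessed by one-way analysis of variance (ANOVA) and compared between every group".

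**The concern.** The article prints its inputs, says the effect size was calculated from them, and gives a value they do not produce. This is the only power justification for the primary outcome. If 0.17 is an f, the trial was sized for a larger effect than the planning data show, and the 80% power belongs to that larger effect. If the planning estimate of 0.62 points is right, a trial with the planned 300 evaluable participants would then be more likely than not to give a non-significant primary result. Anyone relying on the sample-size paragraph would wrongly take that result as evidence from a trial with 80% power against 0.62 points.

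**Working it through.** **Inputs** (Sample size section unless stated): gains 5.50 (SD 2.48) and 4.88 (SD 2.45); two-sided α = 0.05; β = 0.20; 300 evaluable, i.e. 100 per arm; 360 randomised, so 360 × 0.80 = 288, or 96 per arm, after 20% loss; 1:1:1 allocation (Study design). The sham mean is not given, so it is varied below.

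**1. Effect size from the printed inputs**

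- Difference = 5.50 − 4.88 = 0.62
- Pooled SD = √[(2.48² + 2.45²)/2] = 2.465
- d = 0.62/2.465 = 0.252
- f, two groups = d/2 = 0.126
- f, three arms, sham equal to control (or to acupuncture) = d√2/3 = 0.119
- f, three arms, sham midway (5.19) = (d/2)√(2/3) = 0.103

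None equals 0.17. The nearest value found is 0.62/√(2.48² + 2.45²) = 0.178, which leaves out the division by 2 in the pooled variance. It is neither d nor f, and it rounds to 0.18. Whether that slip produced 0.17 is conjecture, and nothing below depends on it.

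**2. What 0.17 would mean**

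- Read as f, the implied acupuncture–control difference is 2 × 0.17 × 2.465 = 0.84 points (two groups), (3/√2) × 0.17 × 2.465 = 0.89 (three arms, sham equal to control), or 2√1.5 × 0.17 × 2.465 = 1.03 (sham midway). These are 35%, 43% and 66% above 0.62.
- Read as d, it is smaller than the inputs give and would need 545 per arm for a two-sample t test.

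**3. The plan's own N**

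A three-group ANOVA with f = 0.17 needs 339 for 80% power. At 300 the power is 75.0%. The other readings of 0.17 tried (two-group ANOVA, two-sample and paired t, correlation, repeated measures) do not give 300 either. That is a separate discrepancy; correcting it would leave the effect-size error in place.

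**4. Power at 0.62 points**

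F test: noncentral F with λ = f²N on 2 and N − 3 degrees of freedom. At N = 300, λ = 0.1186² × 300 = 4.22 (sham equal to control) or 0.1027² × 300 = 3.16 (sham midway).

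Pairwise t test: noncentrality d√(n/2) = 0.2515 × √50 = 1.778 at 100 per arm. The normal approximation is Φ(1.778 − 1.960) = 0.428, and the exact t value is 0.425.

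| Evaluable | F, sham = control (f = 0.119) | F, sham midway (f = 0.103) | Acupuncture vs control t test |
|---|---|---|---|
| 288 (96 per arm) | 41.6% | 32.2% | 41.1% |
| 300 (100 per arm) | 43.1% | 33.4% | 42.5% |
| 360 (120 per arm) | 50.5% | 39.4% | 49.2% |

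The t test column is unadjusted. A Bonferroni correction for three pairwise tests lowers 42.5% to about 26%.

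**5. What 80% power would take**

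- Pairwise t test at 0.62 points: 250 evaluable per arm (750 in total)
- Three-arm F test: 690 in total (sham equal to control) or 918 (sham midway)
- At 96 per arm, the detectable d is 0.406, i.e. 0.406 × 2.465 = 1.00 point, about 60% larger than 0.62

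**The case against.** The arithmetic on the two printed means is not in dispute. The best defence is that the trial has three arms and the third mean is not printed, so a three-arm f of 0.17 is possible. Means of 5.50, 4.88 and 4.48 give f = 0.170, with F-test power of 75% at 300 and 83% at 360. The planning study's control group may not match this trial's health-education arm, and the article also appeals to clinical experience, so an unstated third mean could lie behind the figure. But reaching 0.17 needs a third mean of about 4.48 or 5.90, outside the two printed means, whereas the text presents 0.17 as following from those two. Even then, F-test power at 300 falls short of 80%, and acupuncture versus control stays at 42%.

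A second argument is that the abstract names repeated-measures ANOVA and a mixed model, which can be more efficient. Suppose a correlation of 0.5 between visits and the full 0.62 points at every visit, neither of which the article states. A repeated-measures between-group test then has about 43–63% power at 300, and at most 69% using the two-group f. Baseline adjustment of the pairwise comparison gives about 46–59% at 100 per arm for assumed baseline–follow-up correlations from 0.8 down to 0.3. None reaches 80%.

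What stands is that 33–43% depends on the sham mean lying between the two printed means and on a single-time-point analysis. With no loss at all, the most favourable F-test case in the table is 50.5%, so a non-significant result is then no longer the likelier outcome. How a null result would in fact be interpreted is not stated in the article.

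**Conclusion.** The point holds: 0.17 is wrong as a figure calculated from the stated gains, which give d = 0.25, or f between 0.103 and 0.126. At the plan's own 0.62 points with 300 evaluable, power is 33–43% for the three-arm F test and 42% for acupuncture versus control, roughly half the stated 80%. With 288 evaluable after 20% loss it is 32–42% and 41%. The F-test range assumes a sham mean from 4.88 to 5.50; the pairwise figure needs no assumption about sham. All these figures assume an analysis of eight-week change with the printed SDs. The more efficient models considered raise power but leave it below 80%. This must be corrected, because the primary outcome's power statement rests on it.

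**What to change.** In the Sample size section:

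- Replace 0.17 with the value the inputs give and name its type: d = 0.25, or f with the sham mean stated (f = 0.12 if sham is assumed equal to control, 0.10 if midway). If a different third mean was used, print it and its basis.
- Name the G*Power test and recompute.
- If 360 is kept, state the real power at 0.62 points, about 41–43% with sham equal to control or for acupuncture versus control, and lower if sham lies midway. Alternatively, state that the trial has 80% power for a true difference of about 1.0 MoCA point between two arms at 96 evaluable per arm.
- Do not describe a null result as adequately powered against 0.62 points.

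The cost is rewording one paragraph and accepting a less favourable power statement. No extra participants are needed, and neither the interventions nor the assessments change.

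### The effect size of 0.17 does not follow from the protocol's own MoCA means and SDs; for the printed difference, power is about 41-43%, not 80%

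*Protocol article*

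**What the plan says.** The Sample size section of the protocol article bases the calculation on change in MoCA, the primary outcome. For acupuncture the change "after eight weeks of acupuncture was 5.50 ± 2.48 points", and "the MoCA score difference of the control group was 4.88 ± 2.45 points". It presents the effect size as calculated from these figures: "the calculated effect quantity is 0.17". The error rates are set "by the two-sided test, α = 0.05, β = 0.20", G*Power is named, and the result is that "the sample size is 300 cases". Allowance for loss follows: "Considering the loss of follow-up rate of 20%, the total sample size of this study is 360 cases, i.e., 120 cases in each group".

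The section does not say whether 0.17 is a d or an f, which test was entered, what mean was assumed for the third arm, or whether a correlation between repeated measurements was used. Study design says "the allocation ratio will be 1:1:1", so 300 means 100 per arm. Statistical analysis names one-way ANOVA with comparisons between groups. The Abstract names repeated-measures ANOVA and a mixed linear model.

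**The concern.** The paragraph prints its inputs, its effect size and its sample size, so each step can be checked, and neither step reproduces. The means and SDs do not lead to 0.17 on any usual scale. Nor does 0.17 lead to 300 under the test named in Statistical analysis.

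This paragraph is the only justification for 360 participants. If it stands, a non-significant primary result will be set against a stated 80% chance of detecting 0.62 points, when the chance is about half that. On the printed figures the trial is more likely to miss its planning effect than to find it, and readers of a null result would have no way of knowing.

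**Working it through.** **Inputs** (Sample size; Study design for the allocation): mean change 5.50, SD 2.48; mean change 4.88, SD 2.45; two-sided alpha 0.05; power 0.80; N = 300, or 100 per arm. A 20% loss from 360 leaves 360 × 0.80 = 288, or 96 per arm. (The plan's 360 is 300 × 1.2, whereas keeping 300 after a 20% loss takes 300/0.80 = 375.) Both 96 and 100 per arm are therefore carried through.

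**Step 1: can 0.17 be reproduced?**
- Pooled SD = √[(2.48² + 2.45²)/2] = 2.465.
- d = (5.50 − 4.88)/2.465 = 0.62/2.465 = 0.252.
- Two groups: f = d/2 = 0.126.
- Three groups, third mean equal to either printed mean: f = d × √(2/9) = 0.119. This is the largest f available while the third mean lies within 4.88-5.50.
- Three groups, third mean midway (5.19): f = 0.103.
- The nearest route found is 0.62/√(2.48² + 2.45²) = 0.178. That is not Cohen's f for this design, and it rounds to 0.18.
- A three-group f of 0.17 needs a third mean outside the printed range, about 4.48 or 5.90. Check at 4.48: the grand mean is 4.953, the deviations are 0.547, −0.073 and −0.473, the root mean square is 0.420, and 0.420/2.465 = 0.170. The protocol gives no such mean.

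**Step 2: does 0.17 give 300?** (noncentral F or t, 80% power, two-sided 0.05)
- As f, three-group one-way ANOVA: N = 339; at N = 300, power is 75.0%.
- As f, two groups: N = 274.
- As d, two groups: 545 per group.
- A one-way three-group ANOVA comes close to 300 only with f of about 0.18 (N = 303).

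**Step 3: power from the printed means and SDs**

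| Comparison | 96 per arm | 100 per arm | 120 per arm (no loss) |
|---|---|---|---|
| Pairwise t-test, d = 0.252 | 41.1% | 42.5% | 49.2% |
| Three-group ANOVA, f = 0.119 | 41.6% | 43.1% | 50.5% |
| Three-group ANOVA, f = 0.103 | 32.2% | 33.4% | 39.4% |

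Bonferroni adjustment over three pairs would lower the pairwise figure at 100 per arm to about 26%.

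**Step 4: what 80% power would require**
- Pairwise at d = 0.252: 250 per arm.
- Three-group ANOVA at f = 0.119: 690 in total.
- Detectable pairwise difference at 80% power: 0.98 points with 100 per arm and 1.00 point with 96 per arm (d about 0.40).

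**The case against.** Four arguments can be made for the plan.

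1. **The third mean is unknown and may lie below 4.88.** The section does not say whether its control figure stands for sham or for health education, and the Discussion treats health education as a negative control set up because sham has a placebo effect. With the other two arms at 5.50 and 4.88, three-group ANOVA power at N = 300 is 43% for a third mean of 4.88, 56% at 4.70, 65% at 4.60, 75% at 4.48 and 81% at 4.40. This stands as a caution: 41-43% belongs to the 0.62-point difference, with the third arm at one of the printed means. It does not rescue the paragraph, which presents 0.17 as coming from the two printed means. Nor does any third mean raise power for the pairwise comparison of 5.50 with 4.88.

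2. **The calculation may have been for repeated measures.** With f = 0.17, a three-group between-factor test gives N of 294-306 at an assumed correlation of about 0.75-0.8. That could explain 300 but not 0.17. With f = 0.119, N = 300, two to four measurements and assumed correlations of 0.3-0.8, power is about 47-76%. That test also assumes the full effect at every measurement, which cannot hold if baseline is one of them. So the 339 applies to the one-way ANOVA only.

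3. **Multiple imputation or full retention.** Even all 120 per arm with complete information gives 49-51%.

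4. **Condensed article, unseen analysis plan.** The point concerns figures that are printed and disagree; nothing is alleged to be missing.

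**Conclusion.** The concern holds. The printed means and SDs give d = 0.25 and f of at most about 0.12, not 0.17. The stated beta of 0.20 does not apply to the 0.62-point difference. On those inputs power is 41-43%, so beta is about 0.57-0.59.

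The range assumes 96-100 evaluable participants per arm, an unadjusted comparison of 8-week change at two-sided 0.05 and, for the ANOVA, a third mean equal to one of the two printed means. Full retention raises it to about 50%, and a midway third mean lowers the ANOVA figure to 32-33%. Power near 80% appears only with a third mean, about 4.4, that the protocol does not state, and then only for the overall three-group test.

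**What to change.** Correct the Sample size paragraph:
- State d = 0.25 (f at most about 0.12 for three groups with means within the printed range) in place of 0.17, and name the effect-size scale and the test.
- State that 96-100 evaluable per arm gives about 41-43% power for 0.62 points, and 80% power for a difference of about 1.0 MoCA point.
- If a third arm mean or a correlation between repeated measurements was used to reach 0.17 or 300, state it, say which arm it belongs to, and give its source.
- State in advance that a non-significant primary result will be reported with its confidence interval and not described as absence of effect.

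The cost is a correction to the text and a less favourable stated power. The design and the target of 360 can stay as they are.
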